**Methods/design:**

A 24-week cluster randomized, double-blind, placebo-controlled study will be conducted on 104 adults ≥70 years. Nursing homes will be randomized to either of four groups: Ex-HMB (exercise intervention with HMB), Ex-Plac (exercise intervention with placebo), NoEx-HMB (no exercise intervention with HMB), and Controls (No exercise and no HMB). Intervention groups which include exercise will complete the individualized multicomponent (strength, balance and cardiovascular exercises) training program VIVIFRAIL. Intervention groups which include HMB supplementation will receive a 3 g/daily dose of free acid HMB in powder form. The primary outcome measure is the functional capacity. Secondary outcome measures are muscle strength and power, frailty and fall risk, body composition, biochemical analyses and cardiometabolic risk factor, disability and comorbidity, cognitive function and depression.

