### Eligibility criteria

Inclusion criteria for enrollment will be: men and women aged ≥70 years, be able to follow an active physical rehabilitation program and voluntary participation. Enrollment of cognitively impaired older adults will require proxy permission (family member or caregiver) [41]. All potential participants will provide a medical history and undergo a medical examination to identify cardiovascular or metabolic conditions that would exclude participation (for full list, see Table 1).

**Table 1 Tab1:** Exclusion criteria for the HEAL study

Exclusion criteria	
- Acute heart attack (recent 3–6 months) or unstable angina - Uncontrolled atrial or ventricular arrhythmias - Aortic dissecting aneurysm - Severe aortic stenosis - Acute endocarditis / pericarditis - Uncontrolled high blood pressure (> 180/100 mmHg) - Acute thromboembolism - Acute or severe heart failure - Acute or severe respiratory failure - Uncontrolled postural hypotension - Uncontrolled acute decompensated diabetes mellitus or low blood sugar - A recent fracture in the last month. - Coincident participation in any intervention trial - HMB contraindication, intolerance, or allergy - Have regularly performed exercise (> 20 min > 3 days/week) in the last 3 months - Malignant diseases (exceptions: basal or squamous-cell skin carcinoma or carcinoma in situ of the uterine cervix) - Revascularization within 1 year - Severe loss of vision, hearing, or communicative ability - Conditions preventing cooperation	

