### Sample size

The required sample size will be determined on the basis on the functional capacity, using the Short Physical Performance Battery (SPPB) [42]. According to previous research on subjects with similar characteristics [17], a clinically relevant change is about 1.5 ± 1.0 points increments after 12-weeks. Differences of 2 point in total SPBB with a standard deviation of 3 points with a power of 80% and α of 0.05 can be estimated with 20 participants using the R software (v. 3.2.1) and the package *samplesize*. Assuming a maximum loss of follow-up of 30%, we will recruit 26 adults ≥70 years per group (*n* = 104). Similar interventions had an adherence rate of 75%, and a mean attendance of 80% to the sessions [17]. Therefore, the current estimation is realistic and affordable.

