### Recruitment process and measurements procedures

A schematic overview of the outcomes, measures and timeline is shown in Table 2. Recruitment will be carried out in nursing homes in Murcia (Spain) located within a radius of 15 km or less than 20 min by car from the assessment sites. There are over 15 nursing homes among this radius that ensure recruitment of enough participants. Initial assessment will be carried out in the Human Performance & Sports Science Lab, Faculty of Sport Sciences, University of Murcia (Murcia, Spain). Body composition and biochemical analyses will be performed in the Medical Centre Virgen de la Caridad (Murcia, Spain). Participants will be scheduled in small groups to be taken to the laboratory for the initial assessment and medical centre. Dependent people will be transported in adapted vehicles with a caregiver. All measurements will be performed under technical and medical supervision.

**Table 2 Tab2:** Schedule of enrollment, interventions, and assessments

TIMEPOINT	Enrollment -t_1_	Allocation 0	Baseline t_1_	Intervention	Follow-up 12th week post baseline t_2_	Close-out 25th week post baseline t_3_
ENROLLMENT						
Eligibility screen	✓					
Informed consent	✓					
Randomized Allocation		✓				
INTERVENTION				✓		
Ex-HMB				✓		
NoEx-HMB				✓		
Ex-Plac				✓		
Control				✓		
ASSESSMENTS						
*Functional capacity (primary outcome)*						
SPPB: Gait speed, balance, and 5-sit-to-stand	✓		✓		✓	✓
*Muscle strength and power*						
Grip strength			✓		✓	✓
1RM seated leg press			✓		✓	✓
1RM vertical bench press			✓		✓	✓
Sit-to-stand muscle power			✓		✓	✓
*Frailty and fall risk*						
Frailty phenotype			✓		✓	✓
Falls history	✓		✓		✓	✓
Fall risk assessment	✓		✓		✓	✓
*Body composition*			✓			✓
*Blood pressure and resting heart rate*			✓		✓	✓
*Haematology*			✓		✓	✓
*Biochemical analyses*			✓		✓	✓
*Nutritional status*			✓		✓	✓
*Sarcopenia*			✓		✓	✓
*Disability and comorbidity*						
Barthel index			✓		✓	✓
Lawton index			✓		✓	✓
Comorbidity			✓		✓	✓
*Cognitive function*	✓		✓		✓	✓
*Depression*			✓		✓	✓

Ex: 12-week of VIVIFRAIL multicomponent exercise program. HMB: dietary supplementation of HMB. *Plac* Placebo. *SPPB* Short Physical Performance Battery; *1RM* one-repetition maximum

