*Sarcopenia*: The SARC-F will be used to diagnose sarcopenia [53].

*Disability and comorbidity:* Barthel index [54] and Lawton index [55] will be used to assess disability in basic activities and instrumental activities of daily living, respectively. Given the limitations of comorbidity indexes in older people [56], we will consider comorbidity when a participant presents two or more geriatric syndromes from a list of selected geriatric syndromes, as previously proposed [57].

*Cognitive function and depression:* the validated Spanish version of the Mini-Mental State Examination (MMSE) [58] will be used to assess cognitive function. Depression will be assess with the Spanish version of the 15-item Yeasavage geriatric depression scale [59].

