### Statistical analysis

Analysis will be performed on participants who attended at least 80% the training sessions and completed all the measurements. Treatment effects will be tested using generalized linear models. All models will be adjusted for the baseline outcome value and repeated adjusting for gender, age, the group effect, and confounding factors.

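### Comorbidity, a repeated secondary outcome, is scored only as yes/no at two or more geriatric syndromes, which makes it less sensitive to change than the number of syndromes would be

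*Protocol article*

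**What the plan says.** The abstract's Methods/design paragraph includes this item among the secondary outcomes: "disability and comorbidity, cognitive function and depression". Table 2, introduced under Recruitment process and measurements procedures, ticks the comorbidity row at baseline, at the 12-week follow-up and at close-out in week 25. It is therefore a repeated outcome and not only a baseline descriptor.

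Under Outcome measures, the article gives a reason for avoiding a standard index ("Given the limitations of comorbidity indexes in older people") and then the rule, taken from a cited proposal: "we will consider comorbidity when a participant presents two or more geriatric syndromes from a list of selected geriatric syndromes". It gives no other score for comorbidity and does not list the syndromes.

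The Statistical analysis section tests treatment effects with generalized linear models and adds: "All models will be adjusted for the baseline outcome value". It names no model specific to comorbidity.

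**The concern.** A cut-off at two records only movement between fewer than two syndromes and two or more. Any change that stays on one side of that line is lost. This follows from the rule and needs no outside data.

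How much is lost depends on where residents start. If many start well above two, few can cross the line by gaining or losing one syndrome, and the yes/no baseline value used for adjustment is nearly the same for everyone. What is at stake is interpretation: a null result on an insensitive score could be reported as no effect on comorbidity, and a worsening could be missed in the same way.

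**Working it through.** The article states no figure for comorbidity, so there is nothing to reproduce. The check compares the two ways of scoring the same data.

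**Inputs from the article.** Cut-off: two or more (Outcome measures). Group size: 26 recruited, 20 expected after losses (Sample size). Alpha: 0.05 (Sample size), taken as two-sided.

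**Assumptions, not in the article.** The number of syndromes is Poisson with mean m, treatment lowers the mean by one, and residents are independent. Baseline adjustment is ignored.

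**Share at or above the cut-off.** P(X ≥ 2) = 1 − e^(−m)(1 + m). This gives 26% at m = 1, 59% at m = 2, 80% at m = 3, 91% at m = 4 and 96% at m = 5.

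**Power, 26 per arm.** Two-arm comparisons were simulated, with a t-test on the counts and a two-proportion z-test on the yes/no score:

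| Mean count, control to treated | Controls at two or more | Power, count | Power, yes/no |
|---|---|---|---|
| 2 to 1 | 59% | about 83% | about 68% |
| 3 to 2 | 80% | about 62% | about 39% |
| 4 to 3 | 91% | about 47% | about 20% |
| 5 to 4 | 96% | about 38% | about 8% |

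Repeat runs agree to within about one point.

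**Hand check of the second row (normal approximation).**
- Count: the variance of the difference is (3 + 2)/26 = 0.192, so its standard error is 0.439. 1/0.439 − 1.96 = 0.32, and Φ(0.32) ≈ 0.63.
- Yes/no: the difference is 0.801 − 0.594 = 0.207. Its standard error is √[(0.801×0.199 + 0.594×0.406)/26] = 0.124. 0.207/0.124 − 1.96 = −0.29, and Φ(−0.29) ≈ 0.39.

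**With 20 per arm.** The second row becomes about 50% versus 31% and the last row about 31% versus 5%. The last yes/no figure is no better than alpha.

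**A different effect.** With a 25% reduction in the mean instead of one syndrome, 26 per arm and a normal approximation, power for count versus yes/no is 16% versus 12% at m = 1, 28% versus 19% at m = 2, 39% versus 21% at m = 3, 49% versus 19% at m = 4 and 58% versus 16% at m = 5. The count is ahead at every mean.

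**Why the gap widens.** Of residents at or above the cut-off, only those with exactly two change category by losing one. Under the Poisson assumption that share is 70% at m = 1, 46% at m = 2, 28% at m = 3, 16% at m = 4 and 9% at m = 5.

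**The case against.** A reader might infer that most residents sit above the cut-off throughout, so that the outcome is saturated and cannot register change. The article does not support that.
- It gives no prevalence and no list, and how many residents reach two depends on how long the list is and how strictly each item is defined.
- Eligibility leans towards fitter residents. They must "be able to follow an active physical rehabilitation program and voluntary participation", and severe sensory or communicative loss and conditions that prevent cooperation are excluded. The exercise programme also covers residents with slight or no limitation. Against this, they are nursing-home residents aged 70 or over, and cognitively impaired and seriously limited residents can enter. A high share is plausible but not documented.
- Residents with one or two syndromes can cross the line. Power of 39% in the second row, and 68% in the first, is reduced sensitivity and not incapacity.

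A reader might also infer that the count is already recorded. That is implied, because syndromes must be checked to apply the rule, but it is not stated. An assessor could stop at two.

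Other objections carry weight. The Poisson form and the one-syndrome effect are assumptions: a checklist is bounded and its items may be correlated. Homes are randomised, so treating residents as independent overstates absolute power on either scale. The count itself is below 80% power in three of the four rows. The definition is a published one, chosen for a stated reason. Frailty, falls, nutrition, sarcopenia, disability, cognition and depression are each measured separately, so much geriatric change is captured elsewhere. The article is condensed, and it does not say that the number of syndromes will go unreported.

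These points limit the size and importance of the concern. They do not remove it. The article fixes a dichotomy for a repeated outcome and does not argue that the definition suits the detection of change over 24 weeks. The advantage of the count also remains at the lower prevalences tried.

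**Conclusion.** The point holds as a loss of sensitivity and is minor. The only stated score for this outcome ignores every change that does not cross two syndromes. In all scenarios tried, the count had more power. For a one-syndrome reduction with 26 per arm, the gap was about 15 points when 59% of controls had two or more (83% versus 68%) and about 30 points when 96% did (38% versus 8%).

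The direction does not depend on a ceiling, but the size does. The figures illustrate the comparison under the assumed Poisson count, effect and independence, and do not forecast this trial's power. No primary conclusion is affected.

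**What to change.** State that the number of geriatric syndromes from the same list is the analysed outcome, adjusted for the baseline number. The generalized linear models already planned accommodate a count. Keep the two-or-more indicator as a descriptive or supportive summary, so that the link to the cited definition is not lost.

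The cost is about one sentence. Assessors must complete the full list at every visit and not stop once two syndromes are found, and the count is less directly comparable with work that uses the yes/no definition.

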### Statistical analysis

Analysis will be performed on participants who attended at least 80% the training sessions and completed all the measurements. Treatment effects will be tested using generalized linear models. All models will be adjusted for the baseline outcome value and repeated adjusting for gender, age, the group effect, and confounding factors.

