### Randomization and blinding

After recruitment and baseline measurements, nursing home will be randomized to either of the four groups in clusters, according to a computer-generated sequence using the Sealed Envelope Ltd. online system. The cluster design is chosen to prevent influences on participants’ behaviours within a given nursing home unit. A stratified randomization will be used according to their initial functional status (A, B, C or D, see Fig. 2) to reduce imbalance between groups. The allocation will be concealed in a password protected computer file. Given the nature of the treatment (i.e., daily exercise and dietary supplementation program), participants will be aware of their group allocation. Outcome assessors and data analysts will be blinded to the treatment group assignment. Assessors will not be involved in intervention activities. A dedicated protocol will be defined to protect the confidentiality of data.

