#### Multicomponent physical exercise program

Intervention groups including exercise (Ex-HMB and Ex-Plac) will complete an individualized multicomponent training program, VIVIFRAIL [16], 5 days a week during 24 weeks. Free on-line resources and program guidelines are available online (http://www.vivifrail.com/resources). The VIVIFRAIL program has been carefully designed for people ≥70 years and includes six programs or “Passports” adapted for each participant’s condition according to their functional limitation (serious [A], moderate [B], slight [C] and no limitation [D]) and risk of falling (B+ and C+). Individualization is made based on the baseline testing scores (i.e., the VIVIFRAIL test). Each program combines strength, power, balance, walking, stretching and cardiovascular exercises, in the named “VIVIFRAIL Wheel”. Training sessions are daily and weekly organized (type of exercise, steps and reps) in individual “Passports”. A summary of the exercise program is shown in Fig. 2.

The VIVIFRAIL program has a free mobile app available on iOS and Android, the latest version of which, (launched in January, 2019) allows the recording of the results of the test to automatically assign each participant to a training program. The App includes a calendar with a daily progression, training monitoring and rate of perceiving effort assessment.

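### The only stated analysis set selects on attendance and completion after randomisation, and the attendance condition can act only in the two exercise arms

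*Protocol article*

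**What the plan says.** The protocol article, Statistical analysis, fixes the analysis population in one sentence: "Analysis will be performed on participants who attended at least 80% the training sessions and completed all the measurements". No other set is named in the article, and this one carries no label such as per-protocol, secondary or sensitivity. The same section adjusts all models for the baseline value of the outcome and repeats them with gender, age and other factors.

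The sections that bear on this rule are:

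- **Timing** (Randomization and blinding): "After recruitment and baseline measurements, nursing home will be randomized to either of the four groups in clusters". The same section says that participants will know their group.
- **Who has sessions** (Multicomponent physical exercise program, opening sentence of that section): "Intervention groups including exercise (Ex-HMB and Ex-Plac) will complete an individualized multicomponent training program, VIVIFRAIL [16], 5 days a week during 24 weeks".
- **Who has none** (Abstract, Methods/design): "NoEx-HMB (no exercise intervention with HMB), and Controls (No exercise and no HMB").
- **Expected attendance** (Sample size): "Similar interventions had an adherence rate of 75%, and a mean attendance of 80% to the sessions".
- **Allowance for losses** (Sample size): "Assuming a maximum loss of follow-up of 30%, we will recruit 26 adults ≥70 years per group".

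**The concern.** Attendance and completion are observed after allocation. Restricting the analysis to people who satisfy both gives up the comparability that randomisation provides.

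The attendance condition is also lopsided. NoEx-HMB and Control have no sessions to attend, so read literally the rule would empty both arms. The only workable reading is that it removes people from Ex-HMB and Ex-Plac alone. Good attenders in those arms are then set against residents not selected on attendance.

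The completeness condition applies to all four arms. Read as written, it can remove someone with a valid SPPB because a 1RM test, DXA scan or blood sample is missing.

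What is at stake is the primary outcome in every exercise versus no-exercise contrast. If residents who attend well would have done better anyway, a benefit for exercise would appear with no true effect.

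**Working it through.** **The plan's own figures.** The planning values are "Differences of 2 point in total SPBB with a standard deviation of 3 points with a power of 80% and α of 0.05", and the evaluable number is 20 per group. The recruited number follows as 20 × 1.30 = 26, and 4 × 26 = 104. The only allowance made explicit in that step is the 30% loss to follow-up.

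**Where the threshold falls.** Sessions per exercise participant: 5 × 24 = 120. The 80% rule therefore needs 0.80 × 120 = 96 sessions. The article's expected mean attendance is also 80%, so the cut-off equals the expected mean and substantial exclusion is foreseeable.

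**Share kept in an exercise arm.** The article does not give this. Two readings:

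1. Take the 75% adherence figure as the share meeting the rule (an assumption): 75% kept.
2. Take attendance as Beta-distributed with mean 0.80 and SD 0.10, 0.15 or 0.20 (an assumption): P(attendance ≥ 0.80) = 0.55, 0.58 or 0.62.

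**Number left per exercise arm.**

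- 75% kept, with dropouts among those excluded: 26 × 0.75 = 19.5, about 20.
- Beta reading, with low attendance independent of the 30% dropout: 26 × 0.70 × 0.55 = 10.0, and 26 × 0.70 × 0.62 = 11.3.

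The range is about 10 to 20. It depends mainly on which share is taken and how far dropouts and poor attenders are the same people. The no-exercise arms lose nobody to the attendance condition.

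**Apparent exercise effect when the true effect is zero.** Let q be the share kept, r the correlation between attendance and the SPPB outcome (assumed 0.2 to 0.4), and SD = 3 as in the sample size, before baseline adjustment. Under a normal model:

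bias = r × SD × φ(z)/q, where z is the normal cut-off that leaves a share q above it.

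| Share kept q | φ(z)/q | r = 0.2 | r = 0.3 | r = 0.4 |
|---|---|---|---|---|
| 0.75 | 0.424 | 0.25 | 0.38 | 0.51 |
| 0.62 | 0.614 | 0.37 | 0.55 | 0.74 |
| 0.55 | 0.720 | 0.43 | 0.65 | 0.86 |

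Values are SPPB points, against a planned difference of 2. With r = 0 the bias is zero.

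**Effect of baseline adjustment.** Only the part of the correlation that remains after adjustment matters, and the spread is then smaller. The Sample size section quotes a change of 1.5 ± 1.0 points. If 1.0 is read as the SD of change (an assumption), dividing the table by 3 gives 0.08 to 0.17 points at 75% kept and 0.12 to 0.29 at 55 to 62% kept.

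**Power, to separate two problems.** Two-sample t-test, difference 2, SD 3, two-sided 5% (sidedness assumed), clustering ignored:

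- 10 v 10: 29%
- 10 v 18: 37%
- 18 v 18, with 30% loss and no attendance filter: 49%
- 20 v 20, the planned evaluable number: 54%

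The planned numbers already fall well short of 80% for a two-group comparison before any attendance filter.

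**The case against.** **Attenders as the target.** The article speaks of efficacy, which might seem to justify an adherent population. That would need a comparable control group, and a condition that cannot act in two of the four arms does not supply one. Nor can the matter be left to an unseen analysis plan, because the rule is stated outright.

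**Baseline adjustment.** The models adjust for the baseline outcome. Much of any link between attendance and health may run through baseline SPPB, and the programme is tailored to each resident's limitation. This stands: it reduces the bias, and the bias is conditional on a residual association. It does not remove the asymmetry.

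**Numbers lost.** The authors cite adherence and attendance directly after the 30% allowance, so they may have meant it to cover exclusions under the rule. At 75% kept, about 20 remain, as planned. This stands as a possible reading; 10 per arm is the low end.

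**Completeness.** The condition could mean all time points of the outcome being analysed. That is possible, but the wording does not say so.

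**Stronger readings that a reader might infer.** One is that every HMB effect is estimated only in good attenders. The document does not support this: NoEx-HMB versus Control has no attendance filter. Ex-HMB versus Ex-Plac is filtered on both sides, with indistinguishable supplement packaging, so differential selection is possible but weaker. A second is that the bias is certain and upward. The article gives no data linking attendance to outcome. A third is that the rule is what leaves the trial underpowered. The power figures above show a shortfall without it.

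**Conclusion.** The concern holds in this form: the sole stated analysis set conditions on post-randomisation behaviour, and its attendance part can sensibly act only in Ex-HMB and Ex-Plac. Exercise versus no-exercise contrasts are biased if attendance is related to outcome after baseline adjustment, and the probable direction favours exercise. Ex-HMB versus Ex-Plac is less exposed, and NoEx-HMB versus Control is not filtered on attendance.

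The size cannot be derived from the document. Under the stated assumptions, the spurious effect before adjustment is about 0.25 to 0.5 points at 75% kept and 0.4 to 0.9 at 55 to 62% kept, and less after adjustment. The structural fault does not depend on these figures. Because it affects the primary outcome and is cheap to repair, it should be corrected before analysis.

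**What to change.** Replace the sentence on the analysis population with wording to this effect:

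- The primary analysis includes all randomised participants, analysed by the allocation of their nursing home, using every available SPPB value whatever the attendance.
- The model keeps the planned baseline adjustment and accounts for nursing home.
- Completeness is defined separately for each outcome, so a missing test removes a person only from the analysis of that test.
- The set with at least 80% attendance is kept as a labelled sensitivity analysis, with a statement of how the condition applies to the arms without sessions.

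The cost is one paragraph of text. The estimated effect may be smaller than among attenders only, and residents who stop attending must still be invited to the assessments already scheduled.

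### Nursing homes are randomised, but the stated generalized linear model has no term for within-home correlation, so its nominal 5% tests are anti-conservative by an amount the article does not let one fix

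*Protocol article*

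**What the plan says.** The Abstract and the Study design section both describe a cluster randomised trial. Randomization and blinding makes the unit explicit: "nursing home will be randomized to either of the four groups in clusters". It also gives the reason: "The cluster design is chosen to prevent influences on participants’ behaviours within a given nursing home unit". The authors thus expect residents of one home to affect each other.

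The Statistical analysis section of the Protocol article has three sentences. The first defines the analysed residents: "Analysis will be performed on participants who attended at least 80% the training sessions and completed all the measurements". The second names the model: "Treatment effects will be tested using generalized linear models". The third gives the covariates: "All models will be adjusted for the baseline outcome value and repeated adjusting for gender, age, the group effect, and confounding factors".

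No section mentions a nursing-home term, a random effect, generalized estimating equations (GEE), a cluster-robust variance, a home-level summary, an ICC or a design effect. Recruitment process and measurements procedures says that over 15 homes lie within reach. It does not say how many will be randomised.

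**The concern.** A standard generalized linear model for individual outcomes assumes that residents are independent given the covariates. Residents of one home share staff, diet, routine and each other's company, so their outcomes are likely to be correlated. Because whole homes are allocated, that shared variation goes entirely into the comparison between arms. A model that ignores it gives standard errors and p-values that are too small, and differences between homes can be credited to HMB or to exercise. The section covers all models, so the primary SPPB comparison and the secondary outcomes are both exposed.

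The group effect in the covariate list does not repair this. If it means treatment arm, which is how the article uses the word group, it is the effect under test and not an adjustment. If it means nursing home entered as a fixed effect, homes are nested in arms, the home indicators absorb the arm indicators, and the treatment effect cannot be estimated.

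**Working it through.** **Inputs from the article.** Four arms with the home as randomised unit (Randomization and blinding). Alpha 0.05, 20 participants per group before allowance for losses, and 26 per group recruited, 104 in total (Sample size). Over 15 homes available (Recruitment process and measurements procedures).

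**Inputs assumed, because the article gives none.** ICC 0.01, 0.05 and 0.10. Homes per arm k = 1, 2, 3 and 4; the upper value is about what 15 or so homes would allow over four arms. Homes of roughly equal size.

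**The plan's own figure.** The article states no cluster-related figure, so the only one to reproduce is the sample size: "Differences of 2 point in total SPBB with a standard deviation of 3 points with a power of 80% and α of 0.05 can", the article says, be detected with a sample of 20. For a two-sided comparison of two groups, n = 2 × (1.96 + 0.842)² × 3² / 2² = 35.3, that is 36 per group, not 20. A paired or one-sample t-test does give 20 (power 0.807). The 26 is 20 × 1.3. That mismatch is a separate matter. It matters here only because the calculation contains no design effect, so planning as well as analysis treats residents as independent. The figures 20 and 26 serve below as the range of residents analysed per arm.

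**Step 1, variance inflation.** With m residents per home, m = n/k, the variance of an arm mean is multiplied by DE = 1 + (m − 1) × ICC.

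**Step 2, true error of a naive two-sided 5% test.** α = 2 × [1 − Φ(1.96/√DE)].

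Examples with 26 per arm and ICC 0.05:
- k = 1: DE = 1 + 25 × 0.05 = 2.25, 1.96/1.5 = 1.307, α = 19.1%.
- k = 2: DE = 1 + 12 × 0.05 = 1.60, α = 12.1%.

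**Step 3, the full range (one pairwise test).**

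| Homes per arm | 26 per arm: ICC 0.01 / 0.05 / 0.10 | 20 per arm: ICC 0.01 / 0.05 / 0.10 |
|---|---|---|
| 1 | 8.0% / 19.1% / 29.5% | 7.2% / 16.0% / 25.0% |
| 2 | 6.4% / 12.1% / 18.6% | 6.0% / 10.4% / 15.5% |
| 3 | 5.9% / 9.6% / 14.0% | 5.7% / 8.4% / 11.7% |
| 4 | 5.6% / 8.3% / 11.5% | 5.5% / 7.4% / 9.8% |

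**Step 4, check by simulation.** Four arms, normal outcomes, pooled variance that ignores homes, 20,000 replicates per cell. The pairwise test rejected in 5.3% to 31.2% of replicates over the same range, in line with the formula. The overall test of four groups (3 degrees of freedom) rejected in 5.6% to 55.8%.

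**Step 5, when does the error double?** An error of 10% needs 1.96/√DE = 1.645, so DE = (1.96/1.645)² = 1.42 and ICC = 0.42/(m − 1). With 26 per arm this is 0.017, 0.035, 0.055 and 0.076 for k = 1, 2, 3 and 4. With 20 per arm it is 0.022, 0.047, 0.074 and 0.105.

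**Step 6, what a valid analysis has to work with.** A pairwise comparison of arms with k homes each has 2k − 2 home-level degrees of freedom: 0, 2, 4 and 6 for k = 1, 2, 3 and 4.

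**The case against.** **The size is unknown.** A reader might infer that the error rate is at least roughly doubled. The documents do not support that as a fact, because they give neither the ICC nor the number of homes. At ICC 0.01 the pairwise error never exceeds 8.0%. At ICC 0.05 with 4 homes per arm, which the available homes would permit, it is 7.4% to 8.3%. This objection stands, and only a conditional range can be given.

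**The calculation is not the planned model.** It is unadjusted, while the plan adjusts every model for the baseline value. If homes differ mainly in how frail their residents are at entry, that adjustment may lower the residual ICC. This also stands. The ICCs above should be read as residual ICCs.

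**The article is a summary.** A full analysis plan might add a cluster term, and silence on such detail would be no finding. But the section is not silent: it names the model class and the covariates, and neither accounts for homes. The sample size leaves clustering out as well.

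**The group effect might mean a random home effect.** Its place in the list, "repeated adjusting for gender, age, the group effect, and confounding factors", is odd for the effect under test. But a random home effect would make this a mixed model, which is not what is named. The possibility justifies asking for a definition. It does not make the written analysis valid.

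**One home per arm.** A reader might also infer that each arm has a single home. The article does not say so; that row is one end of an assumed range.

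**Conclusion.** The analysis as written does not match the design and needs correction. Any positive residual ICC pushes the error of the stated test above 5%. Over ICC 0.01 to 0.10, 1 to 4 homes per arm and 20 to 26 residents analysed per arm, one pairwise test has a true error of about 5.5% to 30%. With at least 2 homes per arm the upper end is 18.6%. These figures rest on assumed ICCs and numbers of homes, equal home sizes and no gain from baseline adjustment. That the model lacks a cluster term rests on the article's text alone and is firm; the size of the inflation is not.

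**What to change.** Replace the generalized linear model with one of these:
- a linear mixed model with a random intercept for nursing home (and one for participant if visits are modelled jointly), baseline SPPB as covariate, and Kenward-Roger or Satterthwaite degrees of freedom;
- a home-level analysis adjusted for baseline;
- GEE with a small-sample correction.

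Do not fit homes as fixed effects. Either remove the group effect from the covariates or define it as the random nursing-home effect.

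State the number of homes per arm and the assumed ICC. There must be more than one home per arm: with a single home, treatment and home cannot be separated by any model.

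The analysis change costs new wording and a home identifier in the data. Confidence intervals will be wider, and 2 to 4 homes per arm leave only 2 to 6 home-level degrees of freedom for a pairwise comparison. If any arm was to have a single home, the cost is larger, since recruitment must be spread over more homes.
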